## 12. Statistical parameters

### 12.1. Definition of the analysis sets

We define the following analysis sets used in this study: regular monitoring, interim analysis, main analysis, additional analysis, and final analysis.

#### 12.1.1. All enrolled cases

Among patients enrolled according to “5.1. Enrollment procedures,” the population excluding duplicate enrollments and mis-enrollments is considered as “all enrolled cases.”

#### 12.1.2. Full Analysis Set (FAS)

The Full Analysis Set (FAS) is established as the largest analysis population among all enrolled patients, excluding patients (non-eligible cases) who have been confirmed post facto not to meet the “4. Patient selection criteria” after having received one or more medications. An FAS for the entire study and an FAS for each drug cohort are established.

#### 12.1.3. Safety Analysis Set (SAS)

Out of all registered cases, the population of patients to whom medication has been administered one or more times is defined as the Safety Analysis Set (SAS). An SAS for the entire study and an SAS for each drug cohort are established.

## 12.2. Definition of the endpoints

### 12.2.1. Primary endpoint

The primary endpoint is the response rate based on the best overall effect up to 16±1 weeks after the start of treatment among patients with measurable lesions in the FAS for each drug cohort. Subjects who do not achieve CR/PR by 17 weeks after the start of treatment, and if CR or PR is confirmed for the first time thereafter, are not included in the primary endpoint numerator.

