### 8.3.2. Efficacy endpoints

Perform the imaging evaluation  $16 \pm 1$  weeks after the start of treatment for evaluating the primary endpoint. Moreover, whether or not the imaging evaluation is performed by the 16th week, the frequency of when the imaging evaluation is performed is variable. When a complete response (CR) or partial response (PR) in the overall efficacy is seen for the first time, an additional imaging examination will be conducted in the 4th week thereafter for confirmation. The evaluation is performed according to "11.1. Efficacy evaluation."

During the protocol treatment period, it is desirable to conduct an assessment by contrast CT or

contrast MRI using the same modality and imaging conditions used in the pre-enrollment assessment.

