| Adverse Events                       |           |                       |                  | ◎*7                        |                                       |
| Follow-up                            |           |                       |                  |                            | ◎                                     |

◎: Required, ○: Optional

\*1: Any time before enrollment

\*2: Within 14 days before enrollment

\*3: Select modality according to cancer type

\*4: Within 28 days before enrollment

\*5: Within 28 days before the start of treatment (including the date treatment started)

\*6: Required 16±1 weeks after the start of treatment (otherwise as appropriate)

\*7: From the start of protocol treatment to 30 days after protocol treatment discontinuation or the date of subsequent treatment initiation, whichever comes first. (assess the events to 30 days after treatment discontinuation or the date of initiation of subsequent treatment, whichever comes first). If adverse events are considered to be related to protocol treatment or they are severe regardless of relation to protocol treatment, follow-up will be continued as long as possible until the adverse event is considered

resolved, resolved, or stable.

\*8: Within 14 days after treatment discontinuation date

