## 11. Efficacy assessments

When any treatment is registered in this study, the tumor response effect assessment will be done according to procedures in “The New Guidelines for the Response Evaluation Criteria In Solid Tumors (RECIST guidelines) revised version 1.1 (JCOG Japanese translation revised version 1.1)”(15).

Although the determination interval of overall efficacy is not determined, a comprehensive evaluation is always performed 16±1 weeks after the start of treatment. Furthermore, in this study, we do not collect the details of the efficacy assessments, but collect in the eCRF only the results of the best overall efficacy (11.1.10.) that were confirmed in each treatment.

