### 11.1.5. Tumor response evaluation

16±1 weeks after the start of treatment and at the time of treatment discontinuation, and regardless of whether or not treatment will be prolonged, an evaluation of the target lesions and non-target lesions is to be made according to "8.2. Tests and evaluations during the protocol treatment period" in the same manner as during enrollment, and the diameters of the target lesions and any disappearance or exacerbation of non-target lesions are to be recorded in the chart.

Even if the overall efficacy is determined to be "PD," the protocol treatment is not to be discontinued if it is determined that continuation of the protocol treatment is clinically appropriate, and to continue the protocol treatment even after the overall efficacy is determined as PD, the efficacy determination during this period should be performed according to the following.

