### 11.1.10. Best Overall Response

The overall response is “good” in the order of CR > PR > SD > PD > NE, and the best overall response is determined according to the following criteria. When it corresponds to the definitions of multiple classifications, it is classified as the better one in the order of CR > PR > SD > PD > NE. However, when there are no target lesions at baseline, the best overall response does not use PR, and uses non-CR/non-PD instead of SD.

- **Complete Response (CR):**

When an overall response of CR is obtained two or more times continuously at intervals of 4 weeks (28 days) or more.

Furthermore, the day when the second overall response of CR is confirmed and the best overall effect of CR is determined is the day of confirmed CR.

- **Partial Response (PR):**

When an overall response of PR or better (CR or PR) is obtained two or more times continuously at intervals of 4 weeks (28 days) or more.

Furthermore, the day when the second overall response of PR is confirmed and the best overall effect of PR is determined is the day of confirmed PR.

- **Stable Disease (SD):**

In the case where neither CR nor PR is obtained as the best overall response, and there is at least one overall response of SD or better.

However, the shortest period of SD is 6 weeks from the start of protocol treatment.

- **Progressive Disease (PD):**

When the overall response is PD without corresponding to a best overall response of either CR, PR, or SD.

- **Not Evaluable (NE):**

When all of the overall responses are NE.

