## 12.3. Main analysis and judgment criteria

### 12.3.1. Primary endpoint analysis

In this study, the primary endpoint is the response rate based on the best overall effect up to  $16 \pm 1$  weeks after the start of treatment among patients with measurable lesions in the FAS for each drug cohort. This study is not intended to test hypotheses set in advance, but from the viewpoint of feasibility under the patient-proposed healthcare services, with each drug cohort expected to have up to 50 patients who have measurable lesions as subjects. The main analysis will be conducted for each drug cohort when those 50 patients have been enrolled and the 50th patient has completed the efficacy evaluation up to the time point of  $16 \pm 1$  weeks. For patients who were determined to have measurable lesions at the time of enrollment but for whatever reason the determination was changed to no measurable lesions after treatment started, the best overall response is given as NE.

In this study, it is decided to use Bayesian inference, and if the probability that the posterior distribution of the response rate exceeding the threshold response rate of 60% exceeds 95%, it is determined that the medicine can be expected efficacious. If the corresponding drug is provided free of charge by a company, a report is to be prepared summarizing the information on the drug, and the results of the research shared with the corresponding company, which can then explore the pathway to regulatory approval including clinical trials.

We adopt a beta (0.6, 1.4) with an expected value of 30% as the prior distribution.

In line with the above analysis, 95% confidence intervals (two-sided) are also calculated using an accurate method from frequentist theory (Clopper and Pearson method) based on a binomial distribution for the interval estimates of the response rate.

Furthermore, an interim analysis (12.4.) will be conducted according to the separately established policy based on the data from the time of regular monitoring conducted twice a year.

Even if more than 50 eligible patients with measurable lesions can be enrolled, the same analysis and response as for the main analysis will be performed, and an updated version of the Final Report will be created as an additional analysis of the primary endpoint for each 50 patients, and the results will be examined.

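### The week-17 cut-off, the 28-day confirmation rule and the week-16±1 scan do not fit together, so the primary response numerator can be counted in two ways

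*Protocol*

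**What the plan says.** **Confirmation.** Section 11.1.10 grants a best overall response of CR or PR only when it "is obtained two or more times continuously at intervals of 4 weeks (28 days) or more". The day of confirmed CR or PR is the day of the second determination.

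**Cut-off.** Section 12.2.1 takes the best overall response up to week 16±1. It adds that subjects who have not achieved CR or PR by week 17, "if CR or PR is confirmed for the first time thereafter, are not included in the primary endpoint numerator".

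**Scans.** Section 8.3.2 prescribes imaging at week 16±1 for the primary endpoint. Before that, "the frequency of when the imaging evaluation is performed is variable". The footnote in section 8.6 reads "Required 16±1 weeks after the start of treatment (otherwise as appropriate"; section 11 sets no assessment interval beyond saying that "a comprehensive evaluation is always performed 16±1 weeks after the start of treatment". Two other evaluations are required, both event-driven: one at discontinuation (section 11.1.5: "16±1 weeks after the start of treatment and at the time of treatment discontinuation") and one in the fourth week after a first CR or PR (section 8.3.2).

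**Analysis time.** Section 12.3.1 runs the main analysis of a cohort once 50 patients with measurable lesions are enrolled and "the 50th patient has completed the efficacy evaluation up to the time point of" week 16±1. Section 12.4 applies the same response rate at half-yearly looks.

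**Data.** Section 11 states that "we do not collect the details of the efficacy assessments, but collect in the eCRF only the results of the best overall efficacy".

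**The concern.** The scan prescribed for the primary endpoint falls too late to yield a newly seen response that can be confirmed by the cut-off in section 12.2.1. On the strict reading, whether a responder counts depends on whether the site happened to scan earlier, and the protocol leaves that open. The response rate is then biased downward by an amount that varies with scanning habit as well as with the drug.

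The same count feeds the Bayesian decision in section 12.3.1 and both limits in Table 12.4. A downward bias moves a cohort towards the inefficacy limit and away from the efficacy limit.

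**Working it through.** **1. Timing.**
- Latest first sighting that can be confirmed by week 17: 17 − 4 = week 13.
- The mandatory window runs from week 16 − 1 = 15 to week 16 + 1 = 17, so it opens two weeks after that limit.
- A response first seen at week 15, 16 or 17 is confirmed at the earliest at week 15 + 4 = 19, 16 + 4 = 20 or 17 + 4 = 21. All three fall after the cut-off.
- The scan four weeks after first response and the scan at discontinuation cannot change this, because the 28-day minimum still applies.
- The week-16±1 scan can confirm a response already seen by an optional scan at least 28 days before. It cannot itself start a response that counts on the strict reading. By section 11.1.10 such a patient would stand at SD at the cut-off.

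**2. The plan's own limits.** With the beta(0.6, 1.4) prior, the posterior after r responses in n patients is beta(0.6 + r, 1.4 + n − r). At n = 50:
- r = 37 gives P(rate > 60%) = 0.971, and r = 36 gives 0.944. The efficacy limit is 37.
- r = 5 gives P(rate > 20%) = 0.029, and r = 6 gives 0.069. The inefficacy limit is 5.

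Both agree with Table 12.4. The limits are correct; the fault lies in the count that is compared with them.

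**3. Size on the strict reading.** Let p be the true rate of confirmed response and f the share of those responders first seen at week 16±1. The protocol gives neither, so both are assumptions. The counted rate is p(1 − f), and the number counted is Binomial(50, p(1 − f)).

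| p | Event | f = 0 | f = 10% | f = 20% | f = 30% |
|---|---|---|---|---|---|
| 75% | counted rate | 75% | 67.5% | 60% | 52.5% |
| 75% | P(37 or more of 50) | 0.637 | 0.205 | 0.028 | 0.0015 |
| 80% | P(37 or more of 50) | 0.889 | 0.447 | 0.090 | 0.007 |
| 20% | P(5 or fewer of 50) | 0.048 | 0.093 | 0.168 | 0.281 |
| 30% | P(5 or fewer of 50) | 0.001 | 0.003 | 0.011 | 0.034 |

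**4. The lenient reading.** If first sighting by week 17 is enough, a response first seen at week 16 is confirmed at week 20 or later. The main analysis is triggered by the 50th patient's week-16±1 evaluation. Patients whose first response was seen less than 28 days before the cut cannot yet be confirmed. The same holds at each interim look for the patients most recently evaluated.

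**The case against.** **The strict reading is not the only one.** Section 12.2.1 joins two conditions: no CR or PR achieved by week 17, and confirmation only afterwards. A patient with PR on the week-16 scan has arguably achieved it, so the exclusion would not apply. Week 17 is also the end of the scan window, which suits a limit on first sighting, and section 8.3.2 orders the week-16 scan for this very endpoint. This stands as far as it goes. Against it, section 12.2.1 speaks of confirmation and section 11.1.10 dates a response to the second assessment. The text supports two counts and does not choose between them.

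**Earlier scans are allowed.** Responses first seen by week 13 count on either reading. A reader might infer that the rate is 0% by construction. That would hold only on the strict reading and only for patients with no earlier scan.

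**The data may suffice.** From section 11 a reader might infer that the eCRF holds no response dates and no week-16 value, so that nothing can be checked centrally. The documents do not support that. Sections 14.1 and 14.1.1 plan a central report, from eCRF data, of best overall response up to 16 weeks; measurements stay in the chart, and section 14.2 provides for audits against it. The eCRF layout is not shown. What remains is that the protocol nowhere requires the dates of first and confirmed response to be collected.

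**The consequences are limited.** Section 12.3.1 disclaims any test of a preset hypothesis, crossing a limit in section 12.4 only prompts consideration, and section 12.5 re-analyses all endpoints after follow-up. All true. But the final analysis comes after the main and interim decisions, and it inherits the same unclear numerator.

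**The examples are favourable to the concern.** At a true rate equal to the prior mean of 30%, the inefficacy risk rises only to 0.034 at f = 30%. This stands, and the table shows it.

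**Conclusion.** The timing rules for the primary endpoint are inconsistent as written and need to be reconciled. On the strict reading, responses first seen at week 15 to 17 are lost and the rate is biased downward. On the lenient reading, the main and interim cuts come before the latest confirmations exist.

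The timing conflict follows from the protocol's own numbers and needs no assumption. Its size does: it depends on the assumed f and p and on the strict reading. The loss is serious for a drug near the efficacy limit, material for one near 20%, and small for the inefficacy rule at 30%. Even so, the point should be settled before a cohort is analysed, since it decides who enters the numerator.

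**What to change.** 1. In section 12.2.1, state that CR or PR first documented by week 17 counts if it is confirmed at the next assessment at least 28 days later, even when that falls after week 17.
2. In sections 12.3.1 and 12.4, set the main and interim data cuts after this confirmation window for every patient counted. The earliest confirmation of a week-17 response is week 21.
3. Make sure the dates of first and of confirmed response are recorded, since section 11 commits only to collecting the best overall response.

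The cost is some wording, at most a few eCRF fields taken from the chart, and a main analysis about 5 weeks later per cohort (week 16 to week 21). No extra imaging is implied, because section 8.3.2 already requires the confirmatory scan.

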### 12.2.2. Secondary endpoints

#### 1) Overall survival (OS)

The period from the date of enrollment to the date of death due to any cause

- In the surviving cases, the last survival confirmation date is considered to terminate the case (a survival confirmation can also be made via telephone communication, but it must be recorded in the chart).
- For cases lost to follow-up, termination of the case is made on the last day survival was confirmed before being lost to follow-up.

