#### 8.5. Follow-up

From the time of the first patient enrollment in this study to when the study is completed, follow-ups are performed every 6 months for a period of 3 years to confirm patient survival (in case of death, confirm the date and cause of death), and to confirm any exacerbation (presence and date of any exacerbation, or the date no exacerbation was confirmed). Confirmations of outcome can be done by phone or letter.

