### 10.1. Serious adverse events and events subject to emergency reports

Serious adverse events are those that fall under any of the following. Death

- 1) Diseases, etc. that can lead to death
- 2) Diseases, etc. that require hospitalization or prolongation of hospitalization for treatment
- 3) Disability
- 4) Diseases, etc. that can lead to disability
- 5) Diseases, etc. that are serious according to 1) to 5)
- 6) Diseases or abnormalities that can lead to congenital diseases in later generations

Of these events, those that fall into any of the following categories are defined as serious adverse events for which there is an obligation to provide an emergency report. **1) Death**

- ① [1] Any death that occurs after enrollment and before starting the protocol treatment
- ② Any death during the protocol treatment or within 30 days of the last treatment (whether or not there is a causal relationship with the protocol treatment)
- ③ Death  $\geq 31$  days after the last treatment if a causal relationship with the protocol treatment cannot be ruled out (definite, probable, possible)

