**1) Death or diseases, etc. that can lead to death as provided in 10.1. 1), 2)**

**Primary report:**

The Co-investigator will promptly report the occurrence of a serious adverse event to the Principal Investigator. Having received the report, the Principal Investigator will as soon as possible enter the prescribed items in the “NCCH1901 adverse event report (for facility use)” and in the “Report on a disease, etc.” to be delivered to the Certified Clinical Research Review Board as defined under the Clinical Research Act Enforcement Regulations within 72 hours after learning of the occurrence of the adverse event, and will contact the Study Representative Physician/Study Secretariat by email.

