### 12.3.2. Analysis of efficacy secondary endpoints

Among the secondary endpoints, the efficacy endpoints are overall survival, progression-free survival, and disease control rate. The efficacy analysis set is the FAS for each drug cohort, and analysis is performed for each drug cohort at the time of main analysis or the subsequent primary endpoint analysis. Survival curves, median survival time, and annual survival rates are estimated for each survival time using the Kaplan-Meier method. The 95% confidence intervals (two-sided) are estimated using the Brookmeyer and Crowley method for the respective median survival times. The 95% confidence intervals (two-sided) are calculated using Greenwood's formula for interval estimation of the annual survival rates. An accurate method (Clopper and Pearson method) based on a binomial distribution is used for interval estimates for the disease control rate.

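### At each cohort's main analysis, Kaplan-Meier overall survival may be biased downwards: early deaths are reported at once, survivors are censored at their last confirmation, and no survival update or common cut-off is set

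*Protocol*

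**What the plan says.** - **Deaths.** Protocol 10.1 makes "Any death during the protocol treatment or within 30 days of the last treatment" an emergency report whatever its cause. From day 31 a death is urgent only if a link to the protocol treatment cannot be excluded. Under 10.2.1 the primary report is due "within 72 hours after learning of the occurrence of the adverse event".
- **Survivors.** In 8.5, "follow-ups are performed every 6 months for a period of 3 years to confirm patient survival", by telephone or letter.
- **Censoring.** 12.2.2 states: "In the surviving cases, the last survival confirmation date is considered to terminate the case". It adds that "a survival confirmation can also be made via telephone communication, but it must be recorded in the chart".
- **Timing.** Under 12.3.2, OS "analysis is performed for each drug cohort at the time of main analysis or the subsequent primary endpoint analysis", with Kaplan-Meier curves, medians and annual rates. 12.3.1 triggers the main analysis when 50 patients with measurable lesions are enrolled and the 50th has completed the week 16±1 evaluation. Neither section names a survival update or a common OS cut-off.
- **Other contacts.** The calendar in 8.6 requires imaging at 16±1 weeks and at completion of treatment, and adverse events are recorded to 30 days after discontinuation or the start of the next treatment. Blood tests during treatment are optional. Section 11 says the eCRF holds only the best overall response, not the details of each assessment.

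**The concern.** Kaplan-Meier requires that being censored at a given time says nothing about whether the patient is about to die. The rules above can break this in the interval between a patient's last confirmation and the analysis. A patient who dies on treatment in that interval is entered as an event on the true date. A patient who lives through it is censored at the earlier confirmation and drops out of the risk set. At each such death the factor 1 − d/n has the death in d but lacks some living patients in n, so the curve falls too far.

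At stake are the OS curve, median and annual rates at each cohort's main analysis. For drugs supplied free of charge, 12.3.1 has a report prepared at that point and the results shared with the company, which may then explore a route to approval. Because the error depends on accrual speed and time on treatment, it would also differ between drugs.

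**Working it through.** The protocol gives no assumed OS median, event count or power, so there is no figure of its own to reproduce. The check is a simulation.

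**From the protocol:** 50 patients per cohort (12.3.1); analysis 16 weeks after the last enrollment (approximating the 12.3.1 trigger); deaths on treatment or within 30 days known at once (10.1, 10.2.1); other deaths found at a 6-monthly contact (8.5); survivors censored at the last confirmation (12.2.2).

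**Assumed:** exponential survival with a median of 8 or 12 months (2.1.3 says only that the median is often under one year after standard treatment); uniform cohort accrual over 12, 24 or 48 months; median time on treatment 3 or 6 months; the same death hazard on and off treatment. There were 3,000 runs per setting.

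**True values:** S(12) = 2^(−12/median). This is 2^(−1.5) = 0.354 for a median of 8 months and 2^(−1) = 0.500 for 12 months.

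**Example:** median OS 8 months, 12-month accrual, median treatment 6 months, 6-monthly contacts only. Mean Kaplan-Meier S(12) is 0.280, and 0.354 − 0.280 = 0.074, or 7.4 points low.

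Percentage points by which S(12) reads low (range over both OS medians and both treatment durations):

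| What counts as a confirmation | 12-month accrual | 24-month | 48-month |
|---|---|---|---|
| (a) 6-monthly contacts, clock from each enrollment | 4.8–7.6 | 1.7–2.7 | 0.9–1.3 |
| (a′) 6-monthly calendar sweep from the cohort's first enrollment | 3.8–9.2 | 1.1–2.3 | 0.6–1.0 |
| (b) as (a), plus week-16 scan and discontinuation/30-day contact | 1.1–4.3 | 0.5–1.2 | 0.3–0.7 |
| (c) as (a), plus 4-weekly on-treatment visits | 1.0–1.3 | 0.2–0.5 | 0.2–0.4 |
| (d) deaths and survivors both known only to the 6-monthly contact | within 0.4 of truth | within 0.1 | within 0.2 |
| (e) all statuses confirmed at one cut-off | within 0.2 | within 0.3 | within 0.2 |

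Row (a′) is included because 8.5 counts from the first enrollment in the study and does not clearly set a clock for each patient.

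With a true median of 8 months, the median under (a) reads 6.7–6.8 months with 12-month accrual, 7.4–7.5 with 24 and 7.7 with 48. Under (e) it reads 7.9–8.0. Medians for the 12-month case with 12-month accrual are not used: even (e) gives 10.9 there, because many simulated cohorts never reach their median.

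Row (d) shows that the 6-monthly schedule is not the cause by itself. The cause is the difference in how quickly deaths and survival become known. Rows (d) and (e) correspond to the two remedies, and both remove the bias.

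For scale, the binomial standard error of S(12) with 50 patients is √(0.5 × 0.5 / 50) = 0.071, about 7 points.

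**The case against.** A reader might infer that survivors are confirmed only at 6-monthly contacts and that OS is therefore certainly too low. The text does not support that. 8.5 sets a schedule but does not make it the sole source of alive status, and 12.2.2 accepts any recorded confirmation. Deaths are urgent whatever their cause only during treatment and the following 30 days, and in nearly that same window patients are seen, scanned and assessed for adverse events. From day 31, deaths not considered related are found at the same follow-up as survivors, so a scenario in which every death is known at once is not the protocol's process. The 50th patient has just had a required evaluation when the main analysis is triggered. Crediting 4-weekly visits together with the scan and discontinuation contacts, a separate simulation found 12-month survival at most 0.7 points low.

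It is also fair that censoring at the last date known alive is standard, that 12-month accrual is an assumption (12.4 itself calls accrual uncertain), and that nothing forbids a status update before analysis. OS is descriptive, and no stopping or efficacy rule uses it.

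These points limit the size and certainty of the bias but do not remove it. Four-weekly visits are not required: on-treatment blood tests are optional and imaging frequency is otherwise variable (8.3.2, 8.6). After week 16 the next required scan is at completion of treatment, and assessment dates may not be in the eCRF. A statistical analysis plan, not shown here, could set a cut-off. It could not by itself supply alive-dates that sites were not asked to collect. A standard error of 7 points does not excuse a bias, because the interval is then centred on the wrong value.

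**Conclusion.** The concern holds as a possible downward bias in a descriptive secondary endpoint at each cohort's main analysis, and at additional analyses run the same way. With exponential survival, a median of 8 or 12 months and 12-month accrual, 12-month survival is about 1 to 4 points low if the week-16 and discontinuation contacts count. It is about 4 to 8 points low if only the 6-monthly contacts do, and about 9 in the longer-treatment settings on a calendar clock. With 24 to 48 months of accrual, or frequent recorded on-treatment visits, it is about 1 point or less (up to about 3 with 6-monthly contacts only).

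The simulation covers the 50 patients with measurable lesions. It leaves out those without, who also belong to the cohort's full analysis set. The response rate, the interim rules and the efficacy criterion are unaffected. The final analysis (12.5), run after follow-up of the last patient, largely removes the effect. The change is worth making because it is cheap and the main-analysis results come first.

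**What to change.** In 12.3.2:

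- Set a common OS data cut-off date for each main and additional analysis of a cohort.
- Require the vital status of all cohort patients to be confirmed as of that date. Telephone contact is already accepted in 8.5 and 12.2.2, and a chart record would serve.
- Censor survivors at the cut-off, or at the last contact only if they are truly lost to follow-up, and ignore deaths after the cut-off.
- If no update is done, count both deaths and survival time only up to each patient's last scheduled 6-monthly check.

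The cost is a short addition to 12.3.2 and one phone or chart check per surviving patient at each analysis. The fallback needs no extra contact but gives up some follow-up time.
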